**Figure 1 F1:**
[figure not shown]
A simplified graphic representation of the Markov model with the different health states and the transition possibilities between the health states.

#### Markov states

The Markov states are based on the treatments currently available in the Netherlands. These are: full care centre haemodialysis, limited care centre haemodialysis, home haemodialysis, continuous ambulatory peritoneal dialysis, continuous cyclic peritoneal dialysis, deceased donor kidney transplantation and LDKT. Since transition probabilities and costs may differ over time, that is, a patient who is in his second year of haemodialysis has a different mortality chance than a patient who just started with haemodialysis, we will define separate Markov states for the first year of treatment and subsequent years of treatment for each specific modality. Incident patients who enter the model and prevalent patients who switch between treatment modalities are assigned to the first year Markov states, whereas patients who spend more than 1 year in any health state are transferred to the subsequent years of that same treatment modality.

#### Outcomes

The outcome of the implementation will be compared with the baseline situation; the situation before this programme was implemented. The effect size, in terms of an increase in LDKT, will be used from the RCT conducted earlier. Through sensitivity analyses an estimation can be made of the cost-effectiveness of the intervention whether this assumption is either an underestimation or overestimation. A critical assumption will be the extrapolation of the effects after the 2 years.

### Quality assurance

This study has also implemented a central quality assurance system. We hypothesise that the effectiveness is moderated by the protocol adherence of the team of healthcare professionals. In the implementation study, it might be possible that there are differences in the way teams and centres adhere to the protocol. Protocol adherence measures will be assessed by a third party by means of a telephone interview with the patients and the invitees. Patients and invitees are asked for their opinion and level of satisfaction regarding the way in which the intervention was delivered. Patients and invitees are asked to answer the 15-item TAM scoring list. Items are rated on a Likert scale (1 not at all to 5 very much). Only items that are rated with a 5 will be regarded as fully adherent. Items scored with a 1–4 will be regarded as non-adherent. The outcome of the protocol adherence will be associated with the gain in knowledge and communication skills. We will also look if there is a correlation between the protocol adherence and the amount of LDKTs. A part of the quality assurance is a training that all professionals who conduct the home interventions must take part in. During this training, issues are discussed such as: how to convey uniform and complete information to the patient, how to behave during the home visits, how to create an alignment of the goals of the home visit with the patients, how to assist the patient in inviting friends and relatives, how to deal with emotional moments, how to discuss delicate topics with respect to individual feelings and opinions and, finally, how to ensure no detrimental psychosocial effects of the education occur for the patients and his/her family/friends. All these aspects can be executed in different ways by the educators. A supervisor evaluates the home visits with each team separately every 6 weeks and discuss difficult cases. After these meetings the supervisor is graded by the educators through a 10-item questionnaire regarding the content of the teaching and the interpersonal delivery of the supervisor. Furthermore, the supervisor will bring together all educators for a so-called intervision meeting every 3 months. These intervision sessions are meant to discuss the home visits with each other in order to learn from each other and to keep the procedures similar.

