### Hypotheses

Previous research has provided convincing evidence that transplantation costs less, gives a better survival and a higher quality of life compared with dialysis.^7–9^ We therefore hypothesise that the relatively small incremental costs of the home-based educational programme should be cost-effective. Since it is desirable that in the future all waiting list patients can benefit from the effects of the home-based intervention, this programme should be part of standard care. Hence, a solid basis of the cost-effectiveness of that educational programme is warranted.

The second hypothesis is that higher protocol adherence among healthcare providers will be associated with more positive effects of the educational interventions. These effects include an increase in knowledge of renal disease and the treatment options, an increase in communication with family/friends about RRTs, an increase in living kidney donation activities and an increase in QALYs. If a relationship between protocol adherence and effects is shown, a quality assurance system should be an inseparable part of the educational programme.

The third hypothesis is that a full implementation of the educational programme leads to policy implications regarding care for patients with ESRD. Full implementation may affect the need for dialysis centres and transplantation facilities. By modelling the prevalence we can estimate the need for allocating the healthcare budget. We aim to present the outcomes of the model in a budget impact analysis (BIA).

Thus, the main aim of this article is to discuss the protocol of the cost-effectiveness study of the home-based educational programme and of the quality assurance programme which are currently being implemented in the Netherlands. Additionally, potential policy implications of our hypotheses are discussed in this article.

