## Methods and design

### Participants and procedure

The implementation study is being conducted in the following regions of the Netherlands: Rotterdam, Amsterdam, Nijmegen and Groningen.

The home-based educational programme is currently being implemented in eight hospitals in the Netherlands; four university transplant hospitals and four regional hospitals. Regional hospitals were included to reach those patients who are yet to start RRT and in this setting, this is the target population. In these hospitals, there is a large dialysis unit but no transplants are conducted. For these hospitals, the inclusion criteria are: ≥18 years of age, are eligible for transplantation and primary RRT required within the coming 12 months. In the regional hospitals, allied health professionals carry out the intervention. The four university hospitals incorporate both a dialysis unit and a transplant centre, therefore in this setting both patients who are yet to start RRT and dialysis patients are the target population. Eligible patients for these hospitals are required to be ≥18 years, currently undergoing RRT or required within the coming 12 months and eligible for transplantation. In the university hospitals, allied health professionals are accompanied by psychologists to carry out the intervention. The distinction between the university hospitals and the regional hospitals is in line with the protocols of the aforementioned cross-over study and the RCT. An estimate of the potential candidates for this implementation is about 50 patients per year per university centre and 20 patients per regional hospital. The implementation study will take 2 years.

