### Measures

*Knowledge and communication* are evaluated through questionnaires among all patients and for at least one relative/friend in attendance at the home-based educational session. The knowledge about renal disease and RRTs is measured through a validated knowledge questionnaire R3K-T. This 21-item knowledge questionnaire has been developed specifically for kidney disease, and has good psychometric properties.^13^ Answer categories are multiple choice and the number of correct answers is summed. The three-item communication questionnaire can be answered on a scale from 1 (completely disagree) to 5 (completely agree). An example item is ‘I can talk about renal replacement therapies with my loved ones.’ Finally, we assess patients’ and invitees’ attitude towards RRT through a nine-item questionnaire. This questionnaire can also be answered on a scale from 1 (completely disagree) to 5 (completely agree). An item example is ‘I am afraid donation will harm the health of the donor.’ The administration of questionnaires will take place at two occasions: (1) prior to the education either during an outpatient visit after signing the ‘informed consent form’ or during the first session; and (2) shortly after the second session.

*Protocol adherence measures*: After every completed home intervention an independent telephone evaluation is conducted with the patient and a relative/friend who attended the education programme, to measure the degree of protocol adherence of the educators. The independence is guaranteed through an independent party, specialised in treatment adherence measurement (www.Praktikon.nl). Protocol adherence in this implementation is defined as the extent to which the different teams carry out the educational programme as described in the protocol. Measurement is done with an adaptation of the ‘Treatment Adherence Measures’ (TAM) questionnaire.^14^ TAM is scored on a 0–1 scale, where 1 stands for complete protocol adherence. The results of the TAM can be used for research purposes and to give the educators feedback on the quality of their interventions during the implementation phase.

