### Learning curve

As with all new programmes, educators will inherently experience a learning curve during the first part of the implementation, which could influence the effectiveness of the programme. For instance, the goal of 50 patients per year per academic transplant centre and the goal of 20 patients per regional hospital may not be reached. Regular supervision (on-the-job) training and peer-to-peer coaching may help overcome this, but a learning curve is unavoidable.

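### If adherence and outcomes both improve with educator experience, the planned adherence–outcome association may be partly or wholly spurious, yet a policy conclusion is tied to it

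*Protocol article*

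**What the plan says.** Four parts of the protocol article bear on this point.

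- **Analysis (Quality assurance).** For the questionnaire outcomes: "The outcome of the protocol adherence will be associated with the gain in knowledge and communication skills". For transplants: "We will also look if there is a correlation between the protocol adherence and the amount of LDKTs". No model or covariates are described.
- **Learning curve (Discussion).** The article states that "educators will inherently experience a learning curve during the first part of the implementation, which could influence the effectiveness of the programme". It mentions supervision and coaching as help, "but a learning curve is unavoidable". The example given is that recruitment goals may be missed; the curve is not linked to the adherence analysis.
- **Feedback and supervision (Measures; Quality assurance).** Adherence is measured with the TAM questionnaire. Its results can be used for research and also "to give the educators feedback on the quality of their interventions during the implementation phase". In addition, "A supervisor evaluates the home visits with each team separately every 6 weeks and discuss difficult cases", and all educators meet every 3 months.
- **Inference (Hypotheses).** "If a relationship between protocol adherence and effects is shown, a quality assurance system should be an inseparable part of the educational programme".

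The strengths and limitations list adds that the implementation study has no control group, so the comparison of better- and less-adherent visits is observational.

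**The concern.** A visit late in a team's series differs from an early one in more than its adherence score. The educators have more practice, have been supervised, and may have seen their TAM results. The score is built from ratings by patients and invitees, who are asked for their opinion and satisfaction, so a more assured educator could earn higher ratings and also teach better, whether or not keeping to the protocol matters. Experience would then be a common cause of adherence score and outcome. Because this acts within each team over time, adjusting for hospital or patient mix would not remove it.

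At stake is the reading of the second hypothesis. A relationship produced by general experience would be credited to protocol adherence and carried into advice for insurers and policymakers.

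**Working it through.** The article gives no sample size, power or effect size for this analysis, so there is no figure of the plan's own to reproduce. The check asks how often a simple correlation would be significant if adherence had no effect.

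**Inputs from the article**
- Accrual (Participants and procedure): "about 50 patients per year per university centre and 20 patients per regional hospital", four hospitals of each kind, 2 years.
- With the regional 20 read as per year: 4 × 50 × 2 + 4 × 20 × 2 = 400 + 160 = 560. With it read as a total: 400 + 80 = 480.
- Half the target is 280, used as a low case because the Learning curve section says that the goals may not be reached.

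**Assumed inputs**
- a = correlation of experience (time) with the adherence score; b = correlation of experience with the outcome gain; each varied from 0 to 0.4. The article gives neither.
- Two-sided 5% test. The outcome is treated as a continuous gain; the transplant outcome was not calculated separately.

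**Step 1: spurious correlation.** If experience is the only link between the two, r = a × b.

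**Step 2: chance of a significant result.** With Fisher's z, δ = atanh(r) × √(n − 3), and the rejection rate is Φ(δ − 1.96) + Φ(−δ − 1.96).

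Example, a = b = 0.3, n = 560: r = 0.09, atanh(r) = 0.0902, √557 = 23.60, δ = 2.13. The rate is Φ(0.17) = 0.567; the second term is negligible.

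| a / b | r | n = 560 | n = 480 | n = 280 |
|---|---|---|---|---|
| 0.1 / 0.1 | 0.01 | 5.6% | 5.5% | 5.3% |
| 0.2 / 0.2 | 0.04 | 15.7% | 14.1% | 10.2% |
| 0.3 / 0.3 | 0.09 | 56.7% | 50.4% | 32.4% |
| 0.4 / 0.4 | 0.16 | 96.8% | 94.1% | 76.6% |

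If only one of the two trends, for example a = 0.3 and b = 0, then r = 0 and the rate stays at 5%.

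**Step 3: which adjustment removes it.** Eight teams were simulated (four with 100 patients, four with 40; 2,000 runs; linear time trend; adherence effect zero). The last two rows add independent team effects on adherence and on outcome, each with SD 0.3.

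| a / b | Team SD | Pooled | Team only | Team and time |
|---|---|---|---|---|
| 0.2 / 0.2 | 0 | 16.1% | 16.1% | 4.8% |
| 0.3 / 0.3 | 0 | 58.0% | 56.8% | 5.3% |
| 0.4 / 0.4 | 0 | 96.6% | 96.3% | 5.5% |
| 0.3 / 0.3 | 0.3 | 51.5% | 56.1% | 5.6% |
| 0 / 0 | 0.3 | 10.5% | 5.4% | 5.4% |

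Adjusting for team alone leaves the time-driven false positives in place; team plus time brings them back to about the nominal level. The last row shows why the team term is also needed. The simulation used linear calendar time; a log of visit sequence was not simulated.

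**The case against.** Five objections deserve an answer.

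- **The model is not fixed.** The article speaks only of an association and a correlation. Covariates and clustering are commonly left to an analysis plan, which is not shown, so their absence from a condensed article is not an error. That stands. What the article does fix is the inference: a shown relationship leads to a recommendation, with no condition attached.
- **The premises are possibilities.** A reader might infer that adherence and outcomes will rise together and that a false association must follow. The documents do not support this. The learning curve *could* influence effectiveness and is placed in the first part of the implementation; TAM results *can* be fed back, with no schedule; and the Introduction says that supervision and quality assessment serve to maintain quality, not to raise it. All of this stands.
- **Learning may work through adherence.** If practice improves outcomes because educators follow the protocol better, the association over time is the hypothesised effect. This stands too: bias needs a separate route from experience to outcome. Such a route is plausible given satisfaction-type ratings, but it is not shown.
- **Supervision is itself part of quality assurance.** Gains that it produces would support that system even if adherence were not the mechanism. This stands in part. The conclusion is, however, argued through adherence, and with all teams supervised and no control group the association cannot tell supervision from ordinary practice.
- **Adjustment may remove real signal.** Only a rating of 5 counts as adherent; 1 to 4 do not. With so coarse a score, visit sequence can stand in for true adherence and absorb some of its effect. This stands, and it is why the adjusted estimate should not be shown alone.

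**Conclusion.** The point holds as a conditional one. If adherence scores and outcomes both improve with experience by a route other than adherence itself, the planned association may be partly or wholly spurious, and the article's stated inference offers no protection against that.

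The size depends wholly on the assumed correlations. It is negligible at 0.1/0.1, about three times the nominal rate at 0.2/0.2 with 560 patients (15.7 / 5 = 3.1), and decisive from 0.3/0.3 upwards. Even there the spurious correlation is small: 0.09 is 0.09² = 0.8% of variance. The danger is therefore greatest if statistical significance alone counts as a relationship having been shown.

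The documents do not establish that the bias will occur, nor that the analysis will be pooled and unadjusted. The change is worth making because it is cheap and the conclusion is meant to guide policy.

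**What to change.** 1. Report the association of adherence with each outcome twice: unadjusted, and adjusted for team and for visit sequence within team (or calendar time).
2. Add a sensitivity analysis restricted to visits after a run-in period for each team, with the cut-off set before the data are examined. Any particular cut-off is a judgement, since the article gives no length for the learning curve.
3. Reword the conclusion in the Hypotheses section so that it depends on whether the association persists after adjustment, and say there that the comparison is observational.

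**Cost.** Visit dates and team identity suffice, so no new measurement is needed. Some precision is lost if adherence varies mainly over time, and a true effect may be attenuated because of the coarse TAM scoring. If the two estimates differ, the report should say that the data cannot separate experience from adherence, and should not pick one of them.

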**Methods and design:**

Patients with ESRD who do not have a living kidney donor are eligible to receive the home-based educational intervention. This is carried out by allied health transplantation professionals and psychologists across eight hospitals in the Netherlands. The cost-effectiveness analysis will be conducted with a Markov model. Cost data will be obtained from the literature. We will obtain the quality of life data from the patients who participate in the educational programme. Questionnaires on knowledge and communication will be used to measure the outcomes of the programme. Data on LDKT activities will be obtained from medical records up to 24 months after the education. A protocol adherence measure will be assessed by a third party by means of a telephone interview with the patients and the invitees.

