Given these positive results, a home-based educational programme for patients with ESRD and their social network is currently being implemented in four regions in the Netherlands. Per region, a regional hospital and a university transplant hospital are implementing the programme. The regional hospitals will target patients who are yet to start RRT, while the university hospitals will target both these patients and dialysis patients. The educators organise the intervention in such a way that they will do ‘whatever it takes’, in line with one of the basic principles of multisystem therapy (MST), to make this event as patient tailored as possible.^6^ Supervision and quality assessment are being employed to maintain the quality of the intervention. The first aim of this study is to evaluate the cost-effectiveness of the education to support continued implementation. In this article, we present the study protocol of a cost-effectiveness analysis of the educational programme and its quality assurance system. The patient population, the standard care, the quality of the educations and the setting differ per hospital. Therefore, our second objective is to investigate the relationship between the quality of the implementation of the programme, as measured by protocol adherence, and outcome. Outcome is defined in terms of knowledge, communication and LDKT activities.

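### The adherence analysis is planned as an association with gain and a correlation with LDKT numbers, although patient type and delivery team depend on hospital; it may be confounded and its p-values too small

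*Protocol article*

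**What the plan says.** The Quality assurance section of the protocol article names two analyses of adherence, which is measured by the Treatment Adherence Measures questionnaire (TAM).

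- Questionnaires: "The outcome of the protocol adherence will be associated with the gain in knowledge and communication skills".
- Transplants: "We will also look if there is a correlation between the protocol adherence and the amount of LDKTs".

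It names no unit of analysis, no adjustment variable, no hospital or team term, and no denominator for the number of LDKTs.

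Elsewhere the article describes hospitals that are not alike:

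- The Introduction, as the reason for the second objective: "The patient population, the standard care, the quality of the educations and the setting differ per hospital".
- The Introduction, on case mix: "The regional hospitals will target patients who are yet to start RRT, while the university hospitals will target both these patients and dialysis patients".
- Participants and procedure, on delivery: "In the university hospitals, allied health professionals are accompanied by psychologists to carry out the intervention". No psychologist is mentioned for the regional hospitals.
- Quality assurance, on adherence: "it might be possible that there are differences in the way teams and centres adhere to the protocol".

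The Hypotheses section then says what follows if a relationship is found: quality assurance should become a fixed component of the programme.

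**The concern.** Centre or patient type distorts the adherence-outcome relationship if it is linked to both. The design creates one of these links. Regional hospitals contribute only patients who have not started RRT, university hospitals contribute a mixture, and the article's own earlier studies suggest that the chance of LDKT differs by patient type. The other link, between adherence and hospital, is one that the article itself considers possible. If both hold, a plain correlation mixes hospital differences with any adherence effect.

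Patients are also grouped in eight hospitals. If adherence and LDKT both vary between hospitals, a test that treats patients as independent gives p-values that are too small.

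What is at stake is the second hypothesis and the policy step tied to it. A spurious positive relationship would support quality assurance on weak grounds; a spurious negative one could hide a real benefit.

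**Working it through.** **1. Figure to reproduce.** The article gives no alpha, power or target correlation for this analysis, so there is none.

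**2. Inputs from the article.**
- Patients: 2 years x (4 x 50 + 4 x 20) = 560. If the 20 per regional hospital is a two-year total, 2 x 4 x 50 + 4 x 20 = 480. The checks use 560.
- LDKT in patients yet to start RRT (earlier cross-over study): 34/80 = 42.5%.
- LDKT in dialysis patients (earlier RCT, educated arm): 17 events. Arm sizes are not given. With splits of 82/81 and 83/80, the uncorrected chi-square for 17 versus 4 gives p = 0.0026 and 0.0032, both rounding to the reported 0.003. Assuming 82, the rate is 17/82 = 20.7%.

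**3. Further assumptions.** The dialysis share at university hospitals is 25%, 50% or 75%. Mean TAM differs between hospital types by 0 to 1 SD (within-type SD). Adherence has no effect on LDKT.

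**4. One setting by hand** (75% dialysis; regional TAM higher by 1 SD).
- University LDKT rate: 0.25 x 0.425 + 0.75 x 0.207 = 0.262. Regional rate: 0.425. Difference: 0.163.
- Regional share q = 160/560 = 0.286, so q(1-q) = 0.204.
- Covariance: 1 x 0.163 x 0.204 = 0.0333.
- SD of TAM: sqrt(1 + 0.204) = 1.097.
- Overall LDKT rate: 0.262 + 0.286 x 0.163 = 0.308. SD: sqrt(0.308 x 0.692) = 0.462.
- Expected r = 0.0333 / (1.097 x 0.462) = 0.066.
- Rejection probability: Phi(0.066 x sqrt(557) - 1.96) = Phi(-0.41), about 34%.

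**5. Simulation** (1,000 runs per cell; Monte Carlo standard error at 5% is sqrt(0.05 x 0.95/1000) = 0.7 points). Each cell gives the rejection rate of the plain Pearson correlation, then of the correlation adjusted for centre and dialysis status.

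| Dialysis share | 0 SD | 0.25 SD | 0.5 SD | 1 SD |
|---|---|---|---|---|
| 25% | 5.6% / 5.4% | 6.7% / 6.3% | 6.4% / 5.5% | 7.6% / 5.5% |
| 50% | 5.7% / 5.0% | 6.1% / 4.9% | 9.2% / 5.8% | 18.4% / 4.6% |
| 75% | 5.4% / 4.8% | 6.3% / 3.4% | 14.9% / 4.7% | 34.0% / 4.3% |

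The 34.0% cell agrees with step 4.

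**6. Direction.** In the table regional TAM is the higher, so the spurious correlation is positive. If university TAM is the higher, the sign reverses. With 80% dialysis patients and a 0.5 or 0.8 SD difference that way, separate simulations rejected about 13-14% and 28% of the time, with a negative mean correlation.

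**7. Clustering alone.** The simulations assumed a hospital intraclass correlation for TAM and a hospital SD of LDKT log-odds. Values of 0.10 and 0.5 gave about 8-9% rejection; 0.20 and 0.7 gave about 17-19%.

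**8. Unit of analysis.** If the correlation were taken over eight hospital values, significance would need |r| > 2.447 / sqrt(6 + 2.447^2) = 0.71.

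**9. Gain score.** Let c be the correlation of TAM with baseline score and rho the baseline-to-follow-up correlation, with equal variances and no effect of TAM given baseline. Then corr(gain, TAM) = -c x sqrt((1 - rho)/2). For c = 0.1 to 0.3 and rho = 0.7 to 0.3 (assumed) this runs from -0.04 to -0.18; it is zero if c = 0. The ratio of baseline-adjusted residual variance to gain variance is (1 + rho)/2, which is 0.65, 0.75 and 0.85 for rho = 0.3, 0.5 and 0.7.

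**The case against.** The strongest reply is that this is a condensed article. It does not call the analyses unadjusted, and covariates and clustering may stand in a fuller document that is not shown. That stands as a limit on certainty. It does not remove the point, because the article names the forms of analysis itself, lists hospital differences as the motive for the objective, and attaches a policy step to the result.

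Nothing in the article shows that adherence does differ by hospital type. All educators share training, supervision and peer meetings intended to keep practice alike, and no passage says that a psychologist raises TAM scores. This also stands: with equal adherence the plain test is close to nominal. The 42.5% and 20.7% rates come from separate studies, and the RCT's follow-up is not given.

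A reader might infer that the plan ignores baseline. It does not, because gain subtracts the baseline score. What remains is that gain is not said to be adjusted for baseline level, which biases the result only if TAM is related to that level.

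A reader might also infer unequal follow-up from a two-year study in which "educators will inherently experience a learning curve during the first part of the implementation", so that later and better-delivered sessions are followed for less time. Shorter follow-up would matter: at constant hazard, 42.5% at 24 months is 1 - sqrt(0.575) = 24% at 12 months. But the Abstract sets the window from each patient's education: "Data on LDKT activities will be obtained from medical records up to 24 months after the education". No earlier data cut-off is stated, so this reading is not supported.

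**Conclusion.** The concern holds as a conditional one. The named analyses offer no stated protection against differences that the article itself describes, so the adherence result may be confounded in either direction and its p-value may be too small. It cannot be said that the result is confounded. The false-positive rate for LDKT runs from about 5-6% (no adherence difference between hospital types) through 6-15% (0.5 SD) to about 34% (1 SD with 75% dialysis patients, the most extreme setting in the table). These figures rest on assumed adherence differences, dialysis shares and arm size, and on LDKT rates from two separate studies.

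This should be fixed, but it is not critical. The adherence analysis does not supply the Markov model's effect size, which Table 1 takes from the earlier studies. The Discussion also supports quality assurance on ethical grounds that do not depend on this association.

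**What to change.** In the Quality assurance section:

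- Replace the association with gain by a patient-level model of the post-education score on TAM, adjusted for the baseline score.
- Replace the correlation by a patient-level model of LDKT (yes/no) within 24 months of the education.
- In both, adjust for RRT status at entry and include a hospital random intercept.
- Split TAM into the hospital mean and each patient's deviation from it. Do not add hospital fixed effects, because the hospital-mean term could then not be estimated.

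I would not add calendar time by default, since it may absorb part of the team-level adherence effect of interest. A competing-event analysis should not be promised either, as the article does not show that patient-level deaths and deceased-donor transplants are collected.

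If the analysis is left as it is, the conclusion in the Hypotheses section should be limited to a descriptive association.

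The cost is slightly more analysis, using outcomes, baseline scores and TAM already planned and RRT status known from eligibility. With eight hospitals the between-hospital (team-level) adherence effect will be imprecise, and the text should say so. The adjusted rates in the table used centre indicators with no residual hospital variation; they show that adjustment works in that setting, but the proposed random-intercept model was not itself simulated.
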